**Fig. 2 Fig2:**
[figure not shown]
Schedule for timing of the intervention and different assessments

#### Assessment of primary and secondary outcomes: number of binge free days and other eating disorder pathology

##### EDE

The Eating Disorder Examination (EDE) [28] is a semi- structured interview assessing eating disorder pathology during the last 28 days, including binge eating behavior. The EDE, considered to be the golden standard for eating disorder assessment, has good discriminative and concurrent validity [51], internal consistency [28], and test-retest reliability [52]. Eating disorder symptoms are measured on a 7 point Likert scale [40].

##### EDE-Q

The Dutch version of the Eating Disorders Examination-Questionnaire 6.0 (EDE-Q) [29, 53] will be used to asses eating disorder pathology. The EDE-Q, consists of four subscales: restraint, eating concerns, weight concerns and shape concerns [29]. The Dutch version of the EDE-Q, has good psychometric properties [53]. The EDE-Q is a self-report questionnaire of 36 items, measuring bingeing behavior during the last 4 weeks. Eating pathology will be measured on a 7 point-Likert scale [29].

#### Assessment of secondary outcomes: quality of life and clinical impairment

##### EQ-5D-5L

Quality of life will be measured by the five-level variant of the five-dimensional EuroQol instrument (EQ-5D-5 L) [43]. A Dutch version of the EQ-5D-5 L has been made available [54]. Psychometric properties for the Dutch version are known to be reliable for a set of different countries, including the Netherlands [55].

##### CIA

Due to eating and compensatory behavior as well as concerns regarding shape, weight and eating patterns, eating disorders occur with several psychosocial impairments. In this study, clinical impairment will be assessed through the Clinical Impairment Assessment (CIA) developed by Bohn et al. [44], which differentiates between eating disorder psychopathology and the impairment secondary to ED psychopathology. The CIA assesses clinical impairment across specific areas of life: personal, social and cognitive. The CIA is a 16 item self-report questionnaire, with items rated on a 4 point Likert scale. The Cronbach’s Alpha is .97 and convergence validity .68 [44]. This study will employ the Dutch translation, which has been shown to have good psychometric properties [56].

#### Costs

##### TiC-P

Health care costs and productivity gains/losses will be measured using the TiC-P [57]. The TiC-P is a self-report questionnaire measuring healthcare consumption and production losses as a consequence of psychiatric disorders. The first part of the TiC-P includes 14 structured no/yes questions on the amount of health care utilization. The second part measures productivity gains/losses by measuring absence from work and reduced efficiency of paid and unpaid work [47, 48, 57].

#### Other measures regarding the intervention

##### Demographics

Demographic characteristics, including age, gender, marital status, domestic situation, level of education and occupational/ student status, will be asked of the participants. These socio-demographic characteristics, which will serve as a moderator, will be assessed by phone during the baseline assessment.

##### Therapeutic Alliance (WAI)

Therapeutic alliance will be measured through the Working Alliance Inventory (WAI), a 36- item self-report questionnaire addressing working alliance between patient and therapist. The items are scored on a 7 point Likert scale, resulting in three dimensions: Bonds, Tasks and Goals [50]. The WAI has high internal reliability [58] and Cronbach’s Alpha is 0.95 [59]. In this study, only the patient’s perspective will be assessed.

### Sample size and power calculation

Effects of GSH CBT-E are expected to be comparable to other self-help treatments targeting eating behavior, i.e. a 46% decrease in binge eating episodes with an effect size of Cohen’s *d* = 0.47 between the experimental and control condition [19]. Since self-help treatment for BED has an overall drop-out of 24% [19], 25% more participants are included to obtain sufficient power. Sample size calculation has been conducted using R package ‘pwr’. The sample size without correction is *N* = 144 (*n* = 72 per arm). The sample size corrected for drop-out will be *N* = 180 (*n* = 90 per arm), with a power of 80%, to find an effect size of *d* = 0.47, α = 0.05 (2-sided).

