Studies have shown that several online self-help treatments, including the use of apps on different devices such as smartphones or computers, are effective when combined with therapeutic support [17]. This is also the case for BED [17, 18], and a recent meta-analysis showed that 46% of the individuals classified with BED report not to suffer from binge eating episodes after self-help treatment [19]. There are, however, differences in the efficacy of self-help treatment [18], with guided self-help (GSH) being found to be more effective than non-guided self-help [20], and a stronger therapeutic alliance improving treatment efficacy [21, 22]. The literature further suggests therapeutic alliance to be stronger when contact is synchronous as by phone than when asynchronous as by email [21].

Responding to the absence of CBT-Enhanced based guided self- help (GSH) in Dutch, Novarum, Center for Eating Disorders in the Netherlands, has developed a CBT-Enhanced based GSH (GSH CBT-E), based on the self-help section (Part two) of *Overcoming Binge Eating, The Proven Program to Learn Why You Binge and How You Can Stop* [23]. A study of GSH for BED by Ter Huurne et al., based on general Cognitive Behavioral Therapy (CBT) and Motivational Interviewing (MI), in the Netherlands have shown that, compared to a waiting list condition, an online GSH version of Cognitive Behavioral Therapy (GSH CBT), is particularly effective in reducing eating disorder pathology. At the same time, reduction in binge eating episodes, the main symptom in individuals suffering from BED, has not been reported [24]. Although one GSH CBT study in Germany did show a reduction of binge eating episodes of 58% [25], the treatment protocols used in both studies, in the Netherlands as well as in Germany, were not based on CBT-Enhanced, and a GSH version of CBT-Enhanced is expected to be more effective than GSH CBT [21, 26].

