### Randomization

Randomization will take place after baseline assessment. Dual arm allocation will be performed in a 1:1 ratio, stratified for BMI score. Strata will be defined based on BMI: 19.5 ≥ BMI < 30 or 30 ≥ BMI < 40 by randomly selected block sizes of four, six and eight. Randomization will be performed digitally using Castor EDC (https://www.castoredc.com/) by an independent Arkin data processor not involved in this study. Participants will be informed about their allocation by email by the second author. All other authors will be blinded.

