## Discussion

This paper presents a study protocol of an RCT on the efficacy of online GSH CBT-E treatment for individuals suffering from BED and/or OSFED BED. GSH CBT-E is the first treatment in the Netherlands to follow all NICE [9] guidelines for BED: according to these guidelines is CBT-Enhanced the preferred treatment and that treatment should be offered through the stepped care principle, and recommending guided self-help treatment. The primary goal of GSH CBT-E is to increase the amount of binge free days; secondary goals are to decrease eating disorder pathology and clinical impairment related to the eating disorder and to improve quality of life. Short term efficacy will be assessed directly post treatment, long-term effects will be assessed 12 and 24 weeks post treatment. Direct treatment costs of the intervention will also be calculated.

GSH CBT-E has several strengths. A guided self-help variation of CBT-Enhanced, it meets all recent guidelines for individuals suffering from BED. In addition, since participants can participate in their personal environment, GSH- CBT-E enables individuals to overcome barriers they may experience with face to face treatments, such as stigma, travel time and costs and availability [14–16]. GSH CBT-E will also reduce specialist’s time invested in a single treatment [15]. Based on the number of referrals, we expect to include 12 patients a month, which should be sufficient to result in a final sample size of 180 participants, allowing for a drop-out rate of 25% [19].

This study may also face some challenges. Participants and therapists might not feel comfortable working in an environment that is solely online and phone based due to a lack of face to face contact, or because they might face challenges navigating within the program. Therapists and participants might also experience issues with wireless connection, reception and malware. Therapists may also find it challenging to adapt to the role of guiding self-help therapy rather than providing face to face therapy. Although after the initial session, there is no face to face contact between assessors, therapists and participants, attention will be paid to adverse events, harms or differences in disease state.

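### N = 180 allows for 20% drop-out, not the stated 24–25%; at 24–25% the power is about 77–78% rather than 80%

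*Protocol article*

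**What the plan says.** All references are to the protocol article.

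- **Sample size and power calculation.** The size before correction is 144 (72 per arm), from the R package pwr. Self-help treatment for BED is said to have 24% drop-out overall, and for that reason "25% more participants are included to obtain sufficient power". The corrected size is 180 (90 per arm), "with a power of 80%, to find an effect size of" d = 0.47, with "α = 0.05 (2-sided").
- **Discussion.** Expected recruitment is said to be enough for a "final sample size of 180 participants, allowing for a drop-out rate of 25" per cent.
- **Randomization.** "Dual arm allocation will be performed in a 1:1 ratio", so the two arms are planned at equal size.
- **Background, on a side point.** The source cited for the drop-out rate and effect size is also cited for the statement that "46% of the individuals classified with BED report not to suffer from binge eating episodes after self-help treatment". The sample size section cites the same source and the same 46% as a decrease in binge eating episodes.

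**The concern.** A drop-out rate is a fraction of the people enrolled. The allowance is therefore made by dividing the number needed by the fraction retained. The protocol instead adds a quarter of the number needed. That always gives too small a total, because the loss is then taken from the enlarged sample.

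Two stated figures are affected: the 80% power attached to the corrected size, and the Discussion's statement that 180 covers 25% drop-out. Power is what readers use to judge a non-significant result, so it should follow from the protocol's own inputs.

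**Working it through.** **Inputs, all from the protocol:** d = 0.47; two-sided alpha 0.05; power 80%; 1:1 allocation; 72 per arm before correction; 90 per arm after; drop-out 24% (sample size section) and 25% (Discussion).

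**Step 1. Reproduce the base size.** A two-sample t-test calculation (noncentral t) for d = 0.47, two-sided 0.05 and 80% power gives 72.04 per arm. At exactly 72 per arm, power is 79.98%. The stated 144 is reproduced.

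**Step 2. Reproduce the corrected size.** 144 × (1 + 0.25) = 180, or 90 per arm. This matches exactly, so the rule used was n × (1 + 0.25).

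**Step 3. Apply the retained-fraction rule, N = n / (1 − drop-out).**

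| Drop-out | N to retain 144 | Per arm | Shortfall of 180 |
|---|---|---|---|
| 20% | 144/0.80 = 180 | 90 | 0 |
| 24% | 144/0.76 = 189.5, so 190 | 95 | 10 |
| 25% | 144/0.75 = 192 | 96 | 12 |

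The break-even drop-out for 180 is 1 − 144/180 = 20%, below both rates that the protocol states.

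**Step 4. Power with 180 enrolled** (noncentral t, d = 0.47, two-sided 0.05, equal loss in both arms, drop-outs contributing nothing).

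| Drop-out | Remaining | Per arm | Power | d detectable at 80% power |
|---|---|---|---|---|
| 20% | 180 × 0.80 = 144 | 72 | 80.0% | 0.47 |
| 24% | 180 × 0.76 = 136.8 | 68.4 | 77.9% | 0.483 |
| 25% | 180 × 0.75 = 135 | 67.5 | 77.4% | 0.486 |

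The normal approximation gives 78.5% and 77.9% for the last two rows. The conclusion does not depend on the choice of formula.

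**Step 5. Does the 46% figure enter?** No. Step 1 reproduces 144 from d, alpha and power alone.

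**The case against.** **The loss may not be symmetric.** The cited 24% is drop-out from self-help treatment, and the waiting list arm receives no such treatment before the 12-week primary endpoint. If 24% were lost from the treated arm only (68.4 against 90), power would be 82.9%. With an assumed 10% loss on the waiting list (68.4 against 81) it would be 81.2%. This is fair as a forecast and shows that 77–78% is a cautious figure. It does not rescue the text, because the protocol's own correction enlarges both arms equally, from 72 to 90.

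**Drop-outs may still contribute information.** The Statistical analysis section plans to analyse everyone randomised, with mixed models and multiple imputation. If the model used baseline values, and if the baseline–outcome correlation were 0.25 (both assumptions; the article gives neither), power would be about 80.5% at 24% loss and 79.9% at 25%. This too is fair, but the sample size calculation takes no credit for it. It enlarges the sample because it treats drop-outs as lost.

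**The sentence about 25% more participants is literally true.** It correctly describes going from 144 to 180. The error lies in what is attached to that step: the 80% power after drop-out, and the 25% drop-out rate in the Discussion.

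**The deficit is small.** This stands. Two to three points of power would hardly change how a null result is read, and no test, alpha level, endpoint or procedure is affected.

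**Conclusion.** The point holds as a minor correction. By the protocol's own inputs, 180 delivers the stated 80% power only up to 20% drop-out. At the stated 24–25%, power is 77.9% to 77.4%, the detectable effect rises from d = 0.47 to about 0.483–0.486, and the total is 10 to 12 short of what the stated rates require. These figures assume equal loss in both arms and no information from drop-outs, which is the premise of the protocol's own correction.

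A reader might infer three stronger things that the document does not support:

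- **That the trial is seriously underpowered or must enrol more.** The deficit is 2 to 3 points, and under asymmetric loss or a baseline-adjusted model it could vanish.
- **That the base calculation is wrong.** The 144 is reproduced; only the drop-out step fails.
- **That the conflicting 46% descriptions undermine the sample size.** A proportion free of binge eating and a percentage decrease in episodes are different quantities, so the Background and the sample size section do need reconciling. But the 46% does not enter the calculation, and which description is right cannot be settled without the cited source.

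**What to change.** 1. **Sample size and power calculation.** Restate along these lines: N = 180 gives 80% power for d = 0.47 (two-sided alpha 0.05) if drop-out is at most 20%; at 24–25% drop-out, equal in both arms, power is about 77–78%, and the effect detectable with 80% power is d of about 0.48–0.49.
2. **Discussion.** Change the statement that 180 allows for 25% drop-out in the same way, so that the two sections agree.
3. **Separately,** describe the 46% from the shared source in the same way in the Background and the sample size section, after checking the source. N does not change.

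The cost is wording only, with a slightly less favourable stated power and no extra participants. The alternative is to keep the 80% claim and raise the target to 190 (for 24%) or 192 (for 25%). That means 10 to 12 more participants, about one month at the expected 12 per month. The size of the deficit does not demand it.

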### Randomization

Randomization will take place after baseline assessment. Dual arm allocation will be performed in a 1:1 ratio, stratified for BMI score. Strata will be defined based on BMI: 19.5 ≥ BMI < 30 or 30 ≥ BMI < 40 by randomly selected block sizes of four, six and eight. Randomization will be performed digitally using Castor EDC (https://www.castoredc.com/) by an independent Arkin data processor not involved in this study. Participants will be informed about their allocation by email by the second author. All other authors will be blinded.

### Statistical analysis

The number of binge free days, other eating disorder pathology, quality of life, clinical impairment and therapeutic alliance will be reported as means (standard deviations); and effect sizes between the two conditions will be reported as Cohen’s *d*. Direct costs of the eating disorder treatment will be reported in euros. Cost-effectiveness analysis with number of binge- free days as effect measure and a cost- utility analysis using QALYs will be performed. The QALYs will be derived from the Dutch version of EQ-5D-5 L [43]. Generalized Linear Mixed Models (GLMM) will be used for the analysis of intervention outcomes. The variable BMI 19.5 ≥ BMI < 30 and 30 ≥ BMI < 40 will be included in the GLMM models as covariate. Analyses will be conducted on the entire randomized sample (i.e. intention to treat), and on the per protocol/ treatment completers sample. The primary endpoint for the study is 12 weeks post-randomization. As there are no multiple primary endpoints, there will be no Bonferroni correction or other correction for the significance level applied. Missing data will be handled using multiple imputation. All analyses will be carried out using SPSS version 22+ and R version 3.0+ by an independent Arkin data processor. Results are planned to be published in international peer reviewed journals.

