## Background

Eating disorders, one of the three most common disorders in adolescents [1], have a life time prevalence in the Netherlands of 1.74% [2]. These disorders, which have a significant impact on the psychological and physical well-being of affected individuals [3], are characterized by over-evaluation of shape and weight [4]. Binge eating disorder (BED) is specifically characterized by recurrent episodes of binge eating accompanied by a sense of lack of control [5]. The binges occur at least once a week and, if they are less frequent, the individual is classified with other specified feeding or eating disorder (OSFED) BED [5]. Of the population in the West, 2% suffers from binge eating disorder [6], and 1.5% from OSFED [7].

Of the range of treatments available for eating disorders, including Cognitive Behavioral Therapy (CBT), Dialectical Behavioral Therapy (DBT) and Interpersonal Therapy (IPT), Cognitive Behavioral Therapy-Enhanced (CBT-Enhanced) [8–10] is the preferred evidence based treatment for BED [9]. According to Fairburn, developer of CBT-Enhanced, [11, 12], CBT-Enhanced treatment leads to a recovery rate of 50–65% amongst the individuals with an eating disorder. For BED specifically, the recovery rate is 54% [12]. However, as, according to the stepped care principle, CBT-Enhanced could be too intensive for individuals suffering from BED or OSFED BED, international guidelines have recently recommended guided self-help treatment as first step for individuals suffering from BED [9]. Most online interventions are based on existing face to face treatment protocols [13]. Guided self-help has the advantages of reduced travel costs and travel time for the patient [14], less time of a specialist’s invested in a single treatment [15], and the removal of geographical distance as a barrier to seeking treatment [16]. In addition, an online guided self-help version of CBT-Enhanced (GSH CBT-E) follows all recommended evidence-based guidelines for individuals suffering from BED [9].

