### Participants and recruitment

#### Inclusion

In order to be eligible to participate in this study, a participant must meet the following criteria:
DSM- 5 BED or OSFED BED classification;age at least 18;BMI between 19.5 and 40;moderate proficiency in Dutch and ability to read part one of the Dutch translation of *Overcoming Binge Eating, The Proven Program to Learn Why You Binge and How You Can Stop*, by Christopher Fairburn [34], which involves psychoeducation;willingness to provide contact details, including phone number, internet access, possession of a computer or tablet, and willingness to use it for treatment and research purposes;willingness to sign the informed consent form.

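### The BMI class is the only covariate named for the primary mixed model; the role of baseline binge days is not stated, and stating it would be a free gain in precision

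*Protocol article*

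**What the plan says.** The Statistical analysis section of the protocol article plans generalized linear mixed models, sets the primary time point at 12 weeks after randomization, and names one covariate: "The variable BMI 19.5 ≥ BMI < 30 and 30 ≥ BMI < 40 will be included in the GLMM models as covariate". It says nothing about how the baseline value of an outcome is handled.

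Under Assessment, the EDE interview is scheduled at week 0 and week 12 only. Under Randomization, allocation follows the baseline assessment, so every randomized participant should have a baseline count of binge days. The Background section separates the two eligible diagnoses by binge frequency. BED means at least weekly binges, and "if they are less frequent, the individual is classified with other specified feeding or eating disorder (OSFED) BED".

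The Randomization section defines the strata with the same notation as the model covariate: "Strata will be defined based on BMI: 19.5 ≥ BMI < 30 or 30 ≥ BMI < 40". The Abstract and the Trial design section give the split in words, at a BMI of 30, and the Inclusion list gives eligibility as "BMI between 19.5 and 40".

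**The concern.** The article makes a choice of covariate and names BMI class, which it also uses as the stratification factor. It does not name the pre-randomization value of the primary outcome, usually the first candidate for adjustment. Because BED and OSFED BED are both eligible and randomization is not stratified by diagnosis, the arms could differ by chance in baseline binge frequency. Neither the stratification nor the named covariate addresses that directly.

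At stake is the precision of the primary comparison. With only two EDE time points, the handling of week 0 largely determines the estimator. It can be a plain week-12 comparison, a baseline-adjusted comparison, or a comparison of changes, and these can differ materially in power.

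A smaller matter is that the BMI classes, as typed, do not describe the intended groups.

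**Working it through.** **Inputs from the article (Sample size and power calculation)**
- Effect size and test: "to find an effect size of *d* = 0.47, α = 0.05 (2-sided".
- Power: "with a power of 80" percent.
- Size before drop-out: "The sample size without correction is *N* = 144 (*n* = 72 per arm".
- Drop-out allowance: "self-help treatment for BED has an overall drop-out of 24% [19], 25% more participants are included".

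**Inputs assumed, because the article does not give them**
- r, the correlation between baseline and week-12 binge days: 0.2 to 0.6.
- d = 0.47 is scaled on the unadjusted week-12 SD.
- SDs are equal at both time points (needed only for the change contrast).
- Loss is 25% of 90 per arm: 90 × 0.75 = 67.5.

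**Step 1. Reproduce the stated figure.** A two-sample t-test with d = 0.47, two-sided α = 0.05 and 80% power needs 72.04 per arm. Power at 72 per arm is 79.98%. Then 72 × 1.25 = 90 per arm, and 2 × 90 = 180. The stated numbers reproduce for an unadjusted comparison.

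**Step 2. Unadjusted power after loss.** At 67.5 per arm, power is 77.4%. At the cited 24% loss, 90 × 0.76 = 68.4 per arm and power is 77.9%.

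**Step 3. Baseline as covariate.** Adjustment multiplies the residual SD by √(1 − r²), so the effective effect size is 0.47/√(1 − r²). A model with T0 as a response and a common baseline mean in both arms is essentially equivalent.

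**Step 4. T0 as a response with unconstrained baseline means.** The group-by-time contrast is then a comparison of changes. With equal SDs, the SD of change is √(2(1 − r)) times the week-12 SD, so the effective effect size is 0.47/√(2(1 − r)).

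Power at 67.5 per arm:

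| Assumed r | √(1 − r²) | Effective d, adjusted | Power, adjusted | √(2(1 − r)) | Effective d, change | Power, change |
|---|---|---|---|---|---|---|
| 0.2 | 0.980 | 0.480 | 79.0% | 1.265 | 0.372 | 57.3% |
| 0.3 | 0.954 | 0.493 | 81.1% | 1.183 | 0.397 | 63.0% |
| 0.4 | 0.917 | 0.513 | 84.1% | 1.095 | 0.429 | 69.7% |
| 0.5 | 0.866 | 0.543 | 87.9% | 1.000 | 0.470 | 77.4% |
| 0.6 | 0.800 | 0.587 | 92.3% | 0.894 | 0.525 | 85.8% |

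The change contrast equals the unadjusted comparison at r = 0.5, falls below it for smaller r, and stays below the adjusted analysis throughout this range.

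**Step 5. BMI classes as typed.** Taken literally, the first class requires BMI ≤ 19.5 and the second BMI ≤ 30.

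| BMI | First class, literal | Second class, literal | Class intended by the split at 30 |
|---|---|---|---|
| 19.5 | yes | yes | lower |
| 25 | no | yes | lower |
| 30 | no | yes | upper |
| 35 | no | no | upper |
| 40 | no | no | unclear: excluded by < 40, while the eligibility wording does not say whether 40 itself qualifies |

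**The case against.** The strongest reply is that the article does not exclude baseline from the model. It does not call BMI class the sole covariate. With the EDE at two time points only, a mixed model of EDE binge days has repeated responses per person only if week 0 is one of them. A reader might infer that baseline is not used, but the text does not support that. It supports only that baseline is not named and its role is not stated. A condensed article may also leave such detail to a fuller document. This part of the reply stands. It does not remove the reason to specify the role, because Step 4 shows that having T0 in the model as a response does not by itself secure the gain.

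A reader might also infer that baseline is highly variable and strongly prognostic here. The article gives no SD and no correlation. The mix of BED and OSFED BED suggests spread only qualitatively, and the gain depends on r rather than on spread alone.

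Nor can one say that the planned power is wrong for want of adjustment. The 72 per arm reproduces without it, and omitting a baseline covariate does not bias a randomized comparison. The starting value of 77.4% treats lost participants as contributing nothing, whereas the article plans intention to treat with multiple imputation. The formulas are linear, while the outcome is a day count bounded at 28 and the planned model is a generalized one.

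On BMI, a reader might infer that the strata could not be applied to much of the population. That needs a literal reading which the split in words and the eligibility range contradict. Nothing suggests that the electronic allocation was coded that way.

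**Conclusion.** The point holds as a recommendation to specify, and the improvement is free. The article names BMI class as covariate and leaves the role of baseline EDE binge days unstated, although they are collected before randomization.

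If baseline were left out, the cost would be forgone precision whose size depends on an unknown r. At 67.5 per arm it is about 1.6 power points at r = 0.2 (79.0 − 77.4) and 10.5 at r = 0.5 (87.9 − 77.4). Adjusted power exceeds 80% at r = 0.3 and above, but not at r = 0.2. If baseline were a response with unconstrained means, power would be 57% to 70% for r between 0.2 and 0.4, below the unadjusted 77.4%. All these figures rest on the linear approximation, the assumed 25% loss and the scaling of d stated above.

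The reversed BMI signs are a notation error of little consequence. They have no effect on power if the intended classes are what is coded.

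**What to change.** 1. In Statistical analysis, state that baseline EDE binge days enter the primary 12-week model as a covariate or, if T0 is a repeated response, that the arms share a common baseline mean. Do the same for each secondary outcome with its own baseline.
2. In Randomization and in Statistical analysis, write the classes as 19.5 ≤ BMI < 30 and 30 ≤ BMI, and make the upper bound agree with the eligibility limit so that every eligible BMI has a class.

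The cost is a sentence or two of text. No new data, visits or participants are needed. The first change should be fixed before outcome data are seen by arm.
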